In a period of four and a half years, 425 patients with chronic recurrent tonsillitis, fetor ex ore, swallowing complaints or obstructive complaints due to tonsil hypertrophy underwent a CO2 laser tonsillotomy after informed consent. This showed that patients were able to resume their daily activities and work after an average of 4.2 days. Of the 204 patients who could be followed for a long time (mean 16.8 months, range 1-40) it turned out that 69.6% eventually became completely free of complaints, in 19.1% there was such a reduction in complaints that no further intervention was desired, 10.3% were not free of symptoms after treatment and underwent a classic tonsillectomy. In 2.6% there was minimal bleeding which could be treated conservatively. In 8.6% antibiotics were prescribed shortly after the procedure, but these figures do not fully correspond to reality. In the early years, the GP regularly prescribed antibiotics because of the white discoloration of the wound bed. After better information provision, this number has decreased significantly. In 2010, 117 patients were treated with the laser and antibiotics were prescribed for a wound infection in 4 patients (3.4%). Two patients had a severe vagal reaction to the local anesthetic, causing the procedure to be prematurely discontinued.

A comparison with the classic tonsillectomy was not made in this study. Because of the expected potential of the CO2 laser tonsillotomy, we feel the need to perform a thorough comparative study with the classic tonsillectomy. The aim of this study is to provide more insight into postoperative recovery, effectiveness, complications (both in the short and longer term) and patient satisfaction after CO2 laser tonsillotomy compared to a classic tonsillotomy.

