### 7.5. Study procedure

To evaluate the primary and secondary outcome measures, the patient will be asked to complete a digital evaluation form preoperatively, 2 weeks, 6 months, 1 year and 2 years after the procedure (follow-up study). These forms will be offered by e-mail. In the event of recurrent complaints after the procedure, the patient is asked to go to the ENT doctor /

general practitioner for assessment and to report this to the investigator (by telephone / email). This will also be re-evaluated in the fixed measurement moments.

The operator will fill in a number of questions related to the procedure.

Laser procedure:

- Duration of the laser procedure
- Total duration of outpatient visit
- Amount of local anesthesia administered (number of cartridges)
- Pain during the procedure (VAS score) (patient perception)
- Use of supplemental anesthetic, and the amount thereof
- Coagulation required / not required during procedure
- Complications during surgery

Classic TE procedure:

- Duration procedure (cutting time)
- Duration of hospitalization
- Pain relief administered during surgery (medication, dosage)
- Pain related to procedure (injecting an IV, etc.) (VAS score) (perception pt)
- Coagulation required / not required during procedure
- Complications during surgery

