## 8.2. Analysis

All analyzes will be performed with an intention-to-treat analysis.

A two sided p value  $<0.05$  will be considered significant for all analyses. Survival analysis will be used to compare the primary outcome of recovery time. Survival analysis will also be used to compare time to return to work and postoperative analgesic use. Secondary outcome measures on a continuous scale will be compared using unpaired T-tests or Mann-Whitney U tests, depending on the normality of data (tested using Shapiro-Wilk test). Proportions will be compared using Fisher exact tests.

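### Outcomes collected on repeated forms are assigned single-time two-sample tests; a repeated-measures analysis would use the earlier forms of patients who miss a late one and limit possible bias

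*Protocol*

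**What the plan says.** Protocol section 7.5 asks each patient, for the evaluation of the primary and secondary outcomes, to "complete a digital evaluation form preoperatively, 2 weeks, 6 months, 1 year and 2 years after the procedure (follow-up study" (the quote stops before the closing bracket). On the mode of collection it says: "These forms will be offered by e-mail".

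Section 8.2 then fixes the tests:
- Continuous secondary outcomes: "Secondary outcome measures on a continuous scale will be compared using unpaired T-tests or Mann-Whitney U tests", the choice depending on a normality test.
- Yes/no outcomes: "Proportions will be compared using Fisher exact tests".
- Survival analysis is kept for recovery time, return to work and analgesic use.
- Population: "All analyzes will be performed with an intention-to-treat analysis".
- A two-sided p below 0.05 "will be considered significant for all analyses".

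Section 3 hypothesises that laser effectiveness lies within 30% of that of tonsillectomy. Section 2 reports the sponsor's earlier laser cohort of 425 patients and gives long-term results for a subset: "Of the 204 patients who could be followed for a long time" (mean 16.8 months, range 1 to 40), 69.6% became free of complaints.

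**The concern.** The design yields up to four post-operative forms and one pre-operative form per patient, but the named tests use one value per patient at one time. A patient who answers at 6 months and 1 year but not at 2 years contributes nothing to a 2-year t, Mann-Whitney or Fisher test, although the earlier answers say a good deal about the missing one. If the chance of answering depends on how the patient was doing, the patients left in the two arms are no longer comparable samples of those randomised.

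What is at stake is the long-term effectiveness comparison. The Section 3 hypothesis is one of similarity, so an observed difference that is too small would support the claim for the wrong reason.

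The documents do not list which item sits on which form. That the complaint outcomes recur is read from section 7.5 together with the section 8.1 lists, which record complaints and complaint VAS both before and after surgery.

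**Working it through.** **1. The plan's own figure.** Section 7.4 states 80.2% power for a log-rank test with 95 + 95 patients, medians 8 and 13.5 days, over 14 days. With exponential times:
- Hazard ratio = 8/13.5 = 0.593.
- Expected events = 95 × [(1 − 2^(−14/8)) + (1 − 2^(−14/13.5))] = 95 × (0.703 + 0.513) = 115.5.
- Power = Φ(√(115.5/4) × |ln 0.593| − 1.96) = 80.3%.

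The stated figure is reproduced. It concerns the 14-day recovery endpoint only and has no bearing on the late forms.

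**2. Loss of precision from non-response alone.** Non-response rates are assumed; the documents give none for this trial. With a fraction d missing, the standard error grows by 1/√(1 − d). With 95 per arm, the difference detectable with 80% power is (1.96 + 0.84) × √(2/95) = 0.41 SD.

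| Missing | SE inflation | Power for 0.41 SD |
|---|---|---|
| 10% | 5% | 76% |
| 20% | 12% | 71% |
| 30% | 20% | 65% |
| 40% | 29% | 58% |

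**3. Bias for a VAS score (simulation).** Assumed: 95 per arm, SD 25, true difference 15 points, correlation between forms 0.5 to 0.7, three late forms, permanent drop-out with probability depending on the last observed VAS, and 43 to 50% retained at 2 years. Across independent runs:
- Responder-only 2-year difference: 10.9 to 13.2. Shortfall = (15 − 13.2)/15 = 12% to (15 − 10.9)/15 = 27%.
- Likelihood-based repeated-measures estimate: 14.7 to 15.3.
- Drop-out unrelated to outcome: responder-only 14.9 to 15.0, so no bias.

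A second simulation had milder loss, a true difference of 0.40 SD and a pre-operative form in the model:

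| Drop-out | Retained | Responder-only | Model |
|---|---|---|---|
| Unrelated to outcome | 73% | 0.39–0.40 | 0.40 |
| Depends on earlier score, both arms alike | 63–64% | 0.36–0.38 | 0.41 |
| Poor earlier scores leave, one arm only | 67% | 0.13–0.21 | 0.39–0.40 |
| Good earlier scores leave, one arm only | 72–73% | 0.54–0.58 | 0.39–0.41 |

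So the bias is small when both arms behave alike and retention is fair, and can be large in either direction when the arms behave differently.

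**4. Bias for the yes/no complaint outcome.** Laser 69.6% complaint-free (section 2), tonsillectomy 90% (assumed), true difference 20.4 points. If complaint-free patients respond with probability a and the others with b, the proportion p is seen as p·a/(p·a + (1 − p)·b).
- a = 0.8, b = 0.4: 0.720/0.760 − 0.557/0.678 = 0.947 − 0.821 = 12.7 points.
- a = 0.8, b = 0.6: 0.923 − 0.753 = 17.0 points.
- a = 0.6, b = 0.8: 0.871 − 0.632 = 23.9 points.
- a = 0.4, b = 0.8: 0.818 − 0.534 = 28.4 points.
- a = b: 20.4 points.

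**5. Precision of the model at the same time point.** At 2 years, with SD 25 as in step 3 and loss unrelated to outcome, the model's SE is 4.6 to 5.0 against 5.2 to 5.4 for responders: at the midpoints, (5.3 − 4.8)/5.3, a gain of about 9%. With outcome-dependent loss the two are similar (5.0 to 6.6 against 4.9 to 5.3 in one run). An average over the three late forms is much more precise (3.3 to 3.7), but simply averaging the responder differences gives nearly the same (3.2 to 3.7). That gain belongs to averaging over time, not to the model.

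**The case against.** The strongest reply is that section 8.2 is silent on missing data and on the analysis time point, and that a statistical analysis plan which is not shown may settle both. The named tests could follow imputation, and with complete data, or loss unrelated to outcome, a two-sample test at one time is valid. This stands as far as it goes: the absence of a missing-data method is not the point here. The point is that the protocol itself names the tests, and that they suit outcomes measured once better than outcomes measured repeatedly.

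Three stronger readings are tempting and are not supported:
- **That the plan breaks its intention-to-treat promise.** Comparing patients in their randomised arm with these tests is compatible with that sentence. What is open is how patients without a late form are to count.
- **That the bias favours the laser.** The documents fix no direction. If complaint-free patients fall silent, the difference in proportions grows (23.9 to 28.4 against 20.4) and counts against the laser. It shrinks only if patients with persisting complaints fall silent.
- **That about half the patients will be lost.** 204/425 = 48%, but that cohort was treated over four and a half years with follow-up from 1 to 40 months, and the protocol does not say whether the other 221 were lost or not yet due. It shows that incomplete late follow-up is plausible, not how much to expect here.

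It is also fair to say that an ordinary mixed logistic model gives conditional odds ratios rather than the difference in proportions a 30% hypothesis suggests. The fix allows for this.

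**Conclusion.** The point holds as a cheap improvement to a method that the protocol states. For VAS scores, under assumed heavy loss (about half retained) that depends on the last observed score, the responder-only 2-year difference is about 11 to 13 when the truth is 15; a likelihood-based model recovers about 15. With roughly 63% retained and both arms behaving alike, the shortfall is about 5 to 10% (0.36 to 0.38 against 0.40). With loss unrelated to outcome it is nil, and the precision gain at a single time point is modest.

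For the complaint-free proportion the error can go toward or away from no difference; only the former would flatter the Section 3 hypothesis. All drop-out rates, correlations and the 90% tonsillectomy figure are assumptions. The model removes the bias here because the simulated loss depends on observed scores; it would not fully do so if loss depended on the unseen answer. The primary endpoint and its power are not touched.

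**What to change.** In section 8.2, for outcomes taken from the repeated forms:
- Analyse VAS scores with one linear mixed model per outcome, using all forms of all randomised patients, with arm, time, arm-by-time, indication and the baseline value.
- For the yes/no outcomes, report a model-based difference in proportions that uses the earlier forms, for example by multiple imputation or a longitudinal logistic model with standardised proportions.
- Name one contrast per outcome as the test, for example at 1 year.
- Add one sensitivity analysis for non-response that departs from the assumption that loss depends only on observed data.
- Keep the t, Mann-Whitney and Fisher tests for outcomes measured once.

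The cost is one paragraph and some extra analysis work; no new data are needed. The drawbacks are that the models assume loss depends on observed data, hence the sensitivity analysis, and that results are slightly less simple to report.

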## 8.3. (Statistical) Software

The data will be stored in the databases of the CastorEDC system. The static analysis will be performed using the SPSS software package for Windows, version 24.0.

## 9. Ethical aspects

### 9.1. Regulation statement

This study will take into account the principles related to medical ethics as described by the World Medical Association in the 'WMA Declaration of Helsinki - Ethical Principles for Medical Research Involving Human Subjects (2013)' [19] and as described in the Medical Scientific Research with Humans Act (WMO).

### 9.2. Information provision and informed consent

The patients who are eligible to participate in the study will be informed by the doctor about the advantages and disadvantages of the different interventions. The possibility of conservative medical treatment versus surgery will also be discussed. After providing both oral and written information, the patient is given the opportunity to choose whether to participate in the study. The patient can indicate the time needed to decide whether or not to participate in the study. The maximum reflection period is 2 weeks. Additional information can be found by the patient via our informative website.

### 9.3. Patient insurance

All subjects participating in this study in all participating centers are covered by the WMO subject insurance that has been taken out by the Haga Hospital with Centramed.

### 9.4. Risk Classification

Moderate risk.

## 10. Administrative aspects and publication

### 10.1. Handling and storage of data and documents

The data obtained during this study will be treated confidentially and anonymously. The personal data will be treated in accordance with the Personal Data Protection Act (Wbp). The data will be encrypted where possible and a personal identification code list will be generated. The key to this code will be guarded by the principal investigator. Only the principal investigator and coordinating investigator have access to the source data. Data is kept for a period of ten years.

### 10.2. Amendments

All substantial changes will be communicated to the MREC and must be approved by them before these changes can be put into practice.

A substantial change is defined as a change from the application approved by the MREC that affects:

- the safety of the physical or mental integrity of the participants;
- the scientific value of the study;
- the management of the study;
- the quality or safety of the intervention used in the study

Substantial changes will not be communicated to the MREC.

#### 10.3. Annual progress report

Once a year, the researcher will send a summary of the progress of the process to the accredited MREC. Information about the number of participants, number of participants who completed the study, (S) AEs, changes and problems are communicated.

#### 10.4. End of study report

The researcher informs the accredited MREC within 8 weeks after the end of the study. The end of the study is defined as the last visit of the last study participant. In the event that the study is prematurely terminated, the investigator will inform the MREC of this, including the reasons for this.

Within one year of the end of the study, the investigator will submit a final report with the results of the study. It is expected that at least 2 publications in international journals will follow as a result of this research. These will be sent to the MREC.

### 11. STRUCTURED RISK ANALYSIS

N/A

## 12. Appendices

*Figure 2 : Tonsil size, Friedman classification.*

0. *Status after tonsillectomy*
1. *Tonsils hidden between the pharyngeal arches*
2. *Tonsils extend just outside the pharyngeal arches*
3. *Tonsils enlarged beyond the pharyngeal arches, but not over the median line*
4. *tonsils enlarged to (over) the median line, "Kissing Tonsils"*

[figure not shown]

